**Fig 6 pone.0256323.g006:**
[figure not shown]
Graphical representation of the hypothesized mental training effects. △ = change.

#### Effects of mental training interventions on changes in mediator variables over time during intervention period

We will employ latent growth curve modelling to firstly test changes in daily (pre- and post-daily exercise sessions respectively) and weekly mediator variables over time (unconditional models) and secondly to test the effects of mental training interventions on changes in mediator variables over time (conditional models). Depending on the model fit, latent slope factors will successively be modeled with a linear, quadratic, or freely estimated (only first two factor loadings of growth are constrained) growth over time during the intervention period. Latent intercepts will be modeled with factor loadings at every timepoint constrained to 1. In conditional models, slopes are regressed on group variables (dummy coded for socio-emotional mental training/mindfulness-based mental training) (path a in Fig 6). We will also explore the directional and temporal interplay between the changes in the different mediator variables using different SEM approaches to model daily, weekly and pre-post mediators.

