#### Mental health: Depressive and anxious symptoms

Another area of focus for this phase of the study is to assess intervention-related effects on major mental health outcomes. Therefore, we will examine pre-post changes in depressive and anxious symptoms in our sample using Beck Depression Inventory-II (BDI-II; [113]) and State-Trait Anxiety Inventory (STAI; [114]). Previous studies using MBSR and MBCT have shown significant reductions in these symptoms [115, 116]. Similarly, studies employing socioemotional interventions have shown reductions in symptoms of depression and anxiety [43, 117]. Although the mechanisms through which these changes occur are not fully clear, there is preliminary evidence suggesting the key role of changes in emotion regulation strategies used [72, 118, 119]. Therefore, in the present study, we expect an intervention-related decline in depressive and anxious symptoms, compared to retest control group, owing to a change in use of emotion regulation strategies such as increase in acceptance and decrease in rumination [72, 73, 120]. Further, we will also examine the mechanistic role of other factors that are purported to be involved in the onset and maintenance of depressive and anxious symptoms, namely cognitive control over emotions [121, 122], psychological flexibility [123, 124] social support [125], mindfulness [73, 120], and worry [126]. Furthermore, daily fluctuations in affective states and thought patterns will be evaluated as potential mediators of intervention-related changes in depression and anxiety. Daily fluctuations in affective states will be assessed using the ‘Affect Grid’ [127] which measures both the current valence and the affective arousal. Further, we will use ‘Cube of Thoughts’ [100] to assess the intervention-related changes in valence (positive or negative), temporality (past- or future-oriented) and content (self- or other-related) of thoughts. Previous research has linked fluctuations in affect and thought patterns to be associated with depressive and anxious symptoms [128–131]. We will examine changes in mediators using the daily and weekly EMA approaches, employing a variety of validated questionnaires (please see Measures section). Lastly, we will also examine changes in key mechanisms of negative attention bias and negative interpretation bias that underlie the onset and maintenance of depressive and anxious symptoms [132–134]. Both attention bias and interpretation bias will be assessed using the Mouse-Contingent Scrambled Sentences Task [135].

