#### Retest control group (waitlist control group 3)

The retest control group, which is also a waitlist control group, will only be tested prior to and after the 10-week period at pre-test and post-test wherein other groups undergo the interventions. In a second step, the waitlist control group will then also undergo a 10-week period of socio-emotional intervention, with the exact same protocol as the socio-emotional intervention experimental group 1 described above.

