After the recruitment, participants will complete a 2-week pre-intervention EMA, wherein they will provide saliva samples at specific timepoints and answer questions about their mental and physical health during those corresponding timepoints. This period of data collection will take place at the convenience of participants (at their home, workplace, etc.) to be able to capture the ecologically valid CAR and stress response. For this portion, participants will be sent the appropriate saliva collection kits by mail. Next, all participants will then be invited to the lab to complete the pre-intervention assessment of the behavioral tasks, and they will also complete the pre-intervention assessment of questionnaires using the web and mobile App. This pre-intervention assessment period will last approximately 4 weeks, after which the intervention period will begin.

The intervention period will last 10 weeks, and no blinding will be employed During each week participants in the two intervention groups will perform the intervention-specific exercises 6 times a week using the mobile or web app designed for the study. Every day prior to and after completing the intervention exercise, participants will complete the intervention-related daily EMA using app. Once a week, participants will undergo 2-hour online coaching sessions with an intervention instructor. The purpose of these so-called “weekly check-ins” would be to ensure that participants are able to share insights gained during the week, resolve issues faced during the week, and to keep up the motivation and commitment of participants. Once a week, at a random timepoint, participants will also complete the weekly assessment measures tracking changes in various potential mechanistic variables of interest using the app. During this first intervention period, participants in the retest control group will not complete any daily EMA or weekly assessments. After the completion of the first 10-week intervention period, all participants will again be invited to the lab to complete the same battery of behavioral tasks at post-intervention, and will also complete the same battery of questionnaires through the web and mobile App. Participants will once again undergo a 2-week post-intervention EMA period, during which they will provide saliva samples at specific timepoints, along with answering questions about mental and physical health at those timepoints.

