Upon the completion of the post-test, all participants in the retest control group (waitlist control) will then undergo the 10-week socio-emotional intervention period. Same as above, during each week participants in the waitlist control group will perform the intervention-specific exercise 6 times a week. Every day prior to and after completing the intervention exercise, they will complete the intervention-related daily EMA, and once a week, they will undergo 2-hour coaching sessions with an intervention instructor. They will also complete the weekly assessment measures, once a week at a random timepoint, to track changes in various potential mechanistic variables of interest. The participants will then undergo post-test 2, wherein they will complete the behavioral tasks, pre-post questionnaires, and pre-post EMA. Lastly, post-test 2 will also be offered to participants in the other 2 groups depending upon the availability of resources.

Pre-post questionnaires will be assessed using an online survey which will be implemented in a research WebApp (app.covsocial.de). This WebApp has been developed for the purpose of the CovSocial project. The WebApp and linked Webpage (www.covsocial.de) are developed by the web agency CosmoCode GmbH. Weekly assessments during intervention and daily assessment pre and post daily intervention exercise will also take place through the app.

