#### Effects of mental training interventions on pre-post changes in variables of interest

In order to evaluate intervention-related effects on variables of interest, a mixed-effects modeling approach will be applied. Effects of time of assessment (pre-test/post-test for primary outcome variables and pre-training session/post-training session for secondary outcome variables respectively) and intervention group (socio-emotional mental training/mindfulness-based mental training/waitlist control group), as well as the interaction between time and group will be defined as fixed effects. Dummy coding with the waitlist control group as reference will be used for the intervention group variable. Additionally, we will control for participant-related random effects.

In addition, latent change scores for each primary outcome variable respectively will be computed with two timepoints (pre-test/post-test). The change in outcomes will be modeled as a latent variable and this latent change will be predicted by the treatment condition (path c in Fig 6). A correlation between the latent change score and initial levels on the primary outcome variable of interest is evaluated.

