#### Mediation analysis

The direct effect of the treatment condition on the outcomes of interest (path c’) will be estimated in the SEM framework. The amount of mediation will be indicated by comparison of the direct effect when controlled for the mediator variable (path c’) and the direct effect without controlling for the mediator (path c).

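### Mediation versus waitlist cannot be estimated through daily and weekly slopes that the waitlist arm does not supply, and the plan does not tie paths c and c' to one contrast and one sample

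*Protocol article*

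**What the plan says.** **Mediators.** The protocol article's section on changes in mediator variables states: "We will employ latent growth curve modelling to firstly test changes in daily (pre- and post-daily exercise sessions respectively) and weekly mediator variables over time". For path a, "slopes are regressed on group variables (dummy coded for socio-emotional mental training/mindfulness-based mental training) (path a in Fig 6"). No reference category is given there. The section on associations between changes uses the same latent slopes as predictors of outcome change (path b).

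**Outcome and mediation.** For the latent pre-post change in each primary outcome, "this latent change will be predicted by the treatment condition (path c in Fig 6"). The section Mediation analysis adds: "The amount of mediation will be indicated by comparison of the direct effect when controlled for the mediator variable" and the effect without that control.

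**Data collection.** Under Procedure, during the first intervention period, "participants in the retest control group will not complete any daily EMA or weekly assessments". The section on the retest control group says that this arm "will only be tested prior to and after the 10-week period at pre-test and post-test wherein other groups undergo the interventions". In the second period Procedure says of the same arm: "They will also complete the weekly assessment measures, once a week at a random timepoint". By then it is receiving socio-emotional training.

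**Hypotheses.** The section on depressive and anxious symptoms expects a decline "compared to retest control group, owing to a change in use of emotion regulation strategies". The section on psychological resilience likewise sets mechanism-driven change in the trained groups against the retest control group. Other statements concern differential change between the two trained groups.

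**The concern.** Mediation of a treatment-versus-waitlist effect needs to know how the mediator moved in the waitlist arm. The mediators chosen are trajectories that this arm does not record while it is an untreated comparator. Its later trajectories are recorded under training and cannot stand in.

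The stated hypotheses against the retest control group would then go untested by the stated model. In addition, c could be a three-arm, waitlist-referenced effect while c' is a two-arm, training-versus-training effect. Their difference would be printed as an amount of mediation without belonging to any one contrast.

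**Working it through.** **Inputs.** 300 participants, 100 per group, allocated 1:1:1 (Sample and sampling procedure; Study design and setting). First-period daily and weekly data: socio-emotional 100, mindfulness 100, waitlist 0, before any dropout.

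**The plan's own figure.** The only computed figure is the total of 297 for the group-by-time test. With lambda = f²·N·m/(1−rho) = 0.01 × 297 × 2 / 0.61 = 9.74 on 2 and 294 degrees of freedom, power is 0.8002. At N = 294 it is 0.7959. The figure is reproduced and has no bearing on this point.

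**Step 1: path a with waitlist as reference.** The model is M = a0 + a1·SE + a2·MB.
- Over all 300 people, [1, SE, MB] has rank 3 for 3 parameters.
- Over the 200 with mediator data, SE + MB = 1 for everyone, so the rank is 2 for 3. The null direction is (+1, −1, −1).

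**Step 2: whether full-information likelihood rescues it.** Add Y = c0 + c'1·SE + c'2·MB + b·M. For any shift d, replace:
- a0 by a0 + d, and a1 and a2 by a1 − d and a2 − d;
- c0 by c0 − b·d, and c'1 and c'2 by c'1 + b·d and c'2 + b·d.

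Every observable mean is unchanged, including the waitlist outcome mean c0 + b·a0. The total effect c1 = c'1 + a1·b is identified, but its split is not. With assumed a1 = 0.6, b = 0.5 and c'1 = 0, the indirect effect is 0.30 and the direct effect 0. Taking d = 0.6 gives an indirect effect of 0 and a direct effect of 0.30, with the same fit.

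**Step 3: path a as socio-emotional versus mindfulness.** With one 0/1 variable on 200 people the rank is 2 for 2. Path a is identified, and c and c' are comparable if both are fitted to this contrast in these 200.

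**Step 4: mixing the contrasts.** Assumed for illustration: a = 0.6 (socio-emotional) and 0.3 (mindfulness), b = 0.5, no direct effect, residual SD 1. Expected values are 0.6 × 0.5 = 0.30 and 0.3 × 0.5 = 0.15 versus waitlist, and 0.30 − 0.15 = 0.15 between trained arms. Averages over 2,000 simulated trials:

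| Quantity | Sample | Mean |
|---|---|---|
| c, socio-emotional vs waitlist | 300 | 0.294 |
| c, mindfulness vs waitlist | 300 | 0.142 |
| c, socio-emotional vs mindfulness | 200 | 0.151 |
| c', socio-emotional vs mindfulness | 200 | 0.001 |

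Mixed: 0.294 − 0.001 = 0.293. Matched: 0.151 − 0.001 = 0.150. The mixed figure is about twice the matched one here. The ratio depends wholly on the assumed paths.

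**Step 5: a special case.** Personal disclosure is assessed only after the Affect Dyad (Daily assessment section; Table 1). Group is constant among people with those data, so it has no path a even between the trained arms.

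**The case against.** A reader might infer that path a as coded is not identified. The article does not support that. The sentence on path a names only the two trained groups, and the waitlist reference is stated for the pre-post mixed model. Where the article lists all three groups, it includes the waitlist explicitly. A single socio-emotional versus mindfulness contrast is therefore an available reading, it fits the data-collection schedule, and it is identified. The plural in the path-a sentence leans the other way without settling it. Fig 6, which defines the paths, is not shown and might settle the coding. It could not supply the missing waitlist data.

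It is also fair that the article never says outright that c comes from 300 people and c' from 200, and that much of the mechanism text concerns the trained arms only. But path c carries no restriction, no common sample is stated, and some hypotheses do name the control group. The mixed-model section also applies the three-group factor to measures taken before and after training sessions, which the waitlist arm does not have in that period. So the plan does not consistently allow for the missing arm.

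Two further inferences fail. The absence of a named test for the indirect effect is not a fault, since an article may leave it to the full plan. In linear models on the same people, c minus c' equals a × b. Nor does the waitlist arm lack mediator data altogether: it has the pre-post measures, and daily and weekly data later under training.

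**Conclusion.** The point holds in this form. Mediation versus waitlist through daily or weekly slopes is not estimable, whatever the coding or missing-data method. Mediation between the trained arms is estimable on about 200 people, but it is interpretable only if a, b, c and c' share that contrast and sample, which the article does not fix.

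The size of any distortion cannot be taken from the documents. The doubling shown above rests on assumed paths. The non-identification rests only on the assessment schedule.

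The importance is moderate. Mechanisms are a stated aim and the affected sections need reconciling before analysis. A reader might infer that the trial's efficacy conclusions are at risk, but the three-arm pre-post comparison uses no daily or weekly mediator data from the intervention period and stands as it is.

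**What to change.** 1. **Daily and weekly mediators.** Use one 0/1 group variable in the two trained arms, fit a, b, c and c' in the same participants, and state that the result concerns socio-emotional versus mindfulness only. For personal disclosure, report within-arm association only.
2. **Any mediation claim versus waitlist.** Use baseline-adjusted pre-post change in mediators scheduled in all three arms: for example CERQ, DERS, MAIA, FoC, S-SCS, IRI and the pre-post EMA items. Again fit all paths in one sample.
3. **Mediators measured only weekly or daily.** Drop the versus-waitlist claims. This covers the named mindfulness, worry and psychological-flexibility scales, which are listed only among the weekly assessments.

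**Cost.** Plan wording and some extra modelling, with no new assessments. Pre-post mediators give weaker temporal ordering than weekly slopes, since mediator and outcome change over the same interval. That should be stated as a limitation.

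**One thing to confirm.** Procedure has all participants completing the same pre-post battery, but the section The present study describes the control group as tested only on primary outcomes. Item 2 requires the full battery in that arm.

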#### Associations between changes in outcome variables and changes in mediator variables

In order to evaluate an association between changes in outcome variables and changes in mediator variables over time, latent change scores of primary outcomes and latent slopes of mediator variables will be tested for their correlation. To account for partial mediation, direct paths of latent slopes of mediator variables to latent change scores of primary outcome variables will be estimated (path b in Fig 6).

#### Mediation analysis

The direct effect of the treatment condition on the outcomes of interest (path c’) will be estimated in the SEM framework. The amount of mediation will be indicated by comparison of the direct effect when controlled for the mediator variable (path c’) and the direct effect without controlling for the mediator (path c).

#### Prediction of pretest and intervention-related changes in variables of interest by trait-level individual characteristics and changes in state-levels of vulnerability, resilience and social cohesion

Further, we are interested in exploring whether certain individuals respond better or worse to the interventions based upon specific trait characteristics as well as trajectories of state-level psychological vulnerability, resilience and social cohesion during the course of the pandemic in phase1 (T1-T7). For this, data from phase 1 of the CovSocial project will be used. Phase 1 data has been previously analyzed using a latent factor model approach for trait vulnerability, resilience and social cohesion, and latent change score models for changes in state vulnerability, resilience and social cohesion. Standardized latent factor scores obtained from the trait and state factor models constructed and published in phase 1 (Silveira et al., in preparation) will be used in our current mixed effects modeling approach. Please see preregistration of phase 1 for further details on what indicators constitute the trait and state vulnerability, resilience and social cohesion factors (osf.io/jvb98).

We will examine whether trait predispositions predict mental state at pretest and moderate pre-post intervention changes in the current phase 2 of the project (‘trait effect’). Latent change factors will be employed as outlined above. Observed primary outcome variables at pretest as well as latent changes of those outcome variables will be regressed on the latent trait factors.Next, we will evaluate whether state changes in stress and vulnerability, resilience and social cohesion during the pandemic (T1-T7) can predict state variables of interest at pretest and intervention-related changes in phase 2. Four different models of latent change will be computed using phase 1 data:

“Acute first lockdown effect”: The change in latent factors from pre-lockdown to the first lockdown will be determined using latent change score models (T1-T2 in phase 1)“Recovery effect”: The change in latent factors from the first lockdown to re-opening in Berlin will be determined using latent change score models (T2-T3)“Second lockdown fatigue effect”: The trajectory of change in latent factors during the second lockdown in Berlin will be indicated by the latent slope in latent growth curve models (T4-T7)“Cumulative pandemic effect”: We will compute an unweighted sum of standardized latent change score “acute first lockdown effect” and the standardized latent slope “second lockdown fatigue effect”

Observed primary outcome variables at pretest as well as latent change scores of those outcome variables will be regressed on these latent change scores (acute first lockdown effect, recovery effect), latent slopes (second lockdown fatigue effect), and unweighted sum of the change trajectories (cumulative pandemic effect).

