
An estimated 300 individuals, 100 per intervention group, will be recruited. A priori effect size and power calculations have been performed based on the results from the previous mental training study, the ReSource project [67], which developed and validated the interventions being applied in the current study. Power analyses were conducted using G*Power [194] for analysis of variance with repeated measurements and interactions between group and intra-group variables. The analyses elements were as follows: an alpha level of .05, with a power (1-ß) of .80, 3 groups and 2 measurement occasions, a correlation of variables with repeated measurements of .39 which is the lower limit of retest reliability for the Cortisol Awakening Response (CAR; [195]), and an assumed small effect size of *f* = .10. This results in a total sample size of *n* = 297. For the additional third measurement time (post-test 2 following socio-emotional intervention given to waitlist control group) power analysis was conducted in a similar manner as above.

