#### Background, context and socio-demographic variables

Where necessary, we will account for socio-demographic variables (such as age, gender, marital status, number of children, education in years, and household income) and other context variables including COVID-19 related questions (e.g., access to green spaces, job status, covid-related health status, living situation, financial and job risk factors etc.) assessed in the context of the extensive assessment in phase 1. Predictive value of relevant context- and demographic variables on differences in variables of interest at pretest and their training-related change will be explored similarly to the prediction by latent trait factors assessed in phase 1. Besides, initial levels on outcome variables of interest at pretest will be controlled for by including autoregressive paths in respective models.

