The current study adapts socio-emotional and mindfulness-based interventions applied in the ReSource project (67). The project applied intensive, 3-month long, in-person practice of mindfulness-based and socio-affective interventions that led to enhancement of mental well-being, social capacities such as compassion, empathy and prosocial behaviors, and reductions in a range of vulnerability factors such as stress or negative affect (68). In the current study, we plan to test whether such interventions can be beneficial and have measurable effects when delivered in a less intense, purely app-based online format, with only 12 minutes of practice per day over only a few weeks. This could allow for the development of more flexible forms of such interventions to be able to apply these on a larger scale to heterogeneous population samples. As such, we will validate whether brief, daily 12-minute online interventions that last 10 weeks can lead to prevention of maladaptive outcomes such as depression, anxiety, loneliness and stress, and lead to enhanced resilience, mental well-being as well as increased social competencies and cohesion. This will allow us to ascertain whether large-scale application of such interventions, that require minimal time and effort from participants, is feasible or not in terms of application and outcomes. The findings from the present study will also allow us to test whether such brief interventions can be applied to more clinical settings to reduce incidence of development of psychological disorders, such as major depression and generalized anxiety, in the face of more global stressors. Also, two associated questions of interest that will be answered are a) which type of mental training intervention is specifically effective in bringing about changes in which outcomes, and b) whether specific risk groups benefit more from one specific type of mindfulness-based or socio-emotional intervention. Moreover, the study will also clarify whether the biological embedding of stressful experiences, in the form of genotypic and polygenic risk markers of vulnerability, resilience and social cohesion, can be changed or reversed upon undergoing mindfulness-based and socio-emotional interventions. Lastly, the present study will also serve to advance the field of digitalized and personalized mental health interventions, which is increasingly being seen as an alternative to more traditional forms of in-person psychotherapy and interventions.

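### The analyses of who responds to the trainings are written as regressions of change on the predictor without a predictor-by-group term, so as written they estimate prognosis and not differential response

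*Protocol article*

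**What the plan says.** All places are in the Protocol article.

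- **Aim.** The section on prediction of pretest and intervention-related changes sets out to explore "whether certain individuals respond better or worse to the interventions". It says that traits will be examined as predictors of the pretest state and as moderators of pre-post change.
- **Claim.** The Discussion lists, among the questions the study will answer, "whether specific risk groups benefit more from one specific type of mindfulness-based or socio-emotional intervention".
- **Model for traits.** "Observed primary outcome variables at pretest as well as latent changes of those outcome variables will be regressed on the latent trait factors".
- **Model for the four phase 1 trajectory measures** (first lockdown, recovery, second lockdown, cumulative). "Observed primary outcome variables at pretest as well as latent change scores of those outcome variables will be regressed on these latent change scores", and likewise on the latent slopes and on the unweighted sum.
- **Model for context and demographic variables.** Their predictive value "will be explored similarly to the prediction by latent trait factors assessed in phase 1". The same section adds that pretest levels are controlled by autoregressive paths.
- **Where group enters.** Only in the section on pre-post effects of the interventions. There, a mixed model has time, group and their interaction, and a latent change model has treatment condition as a predictor of change. No predictor from phase 1 appears in either.

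**The concern.** Whether someone responds better to a training than someone else is a statement about the difference between trained and untrained change, compared across levels of the predictor. It needs a predictor-by-group contrast. A regression of change on the predictor alone answers something else: who changes more over the ten weeks, for whatever reason. People in the waitlist arm also change, and some traits or pandemic histories will predict that change.

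Two errors can follow. A variable that predicts change equally in all three arms can be read as predicting response to training. A variable that helps in one training and hinders in the other can average out and be missed. The waitlist arm exists to separate natural change from training effects, and these regressions as written do not use it for that. The first half of the written models, pretest level on the predictor, is not affected: no treatment has been given at that point.

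**Working it through.** **1. The plan's own figure.** The sample size section gives "an alpha level of .05", "with a power (1-ß) of .80", "3 groups and 2 measurement occasions", a repeated-measures correlation of .39 and f = .10, leading to n = 297. For the group-by-time interaction:

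- Noncentrality: λ = f² · N · m / (1 − ρ) = 0.01 × 297 × 2 / 0.61 = 9.74
- Degrees of freedom: (3 − 1)(2 − 1) = 2 and (297 − 3)(2 − 1) = 294
- Power: 0.8002 at N = 297, the smallest N that reaches .80, and 0.8044 at N = 300

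The figure reproduces. It covers the group-by-time test only and says nothing about moderators.

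**2. What the written regression estimates.** Let b_W, b_S and b_M be the slopes of change on a standardised predictor in the waitlist, socio-emotional and mindfulness arms. With equal arms and a common slope fitted across them, the coefficient estimates the mean, (b_W + b_S + b_M)/3. Differential response is the set of differences b_S − b_W, b_M − b_W and b_S − b_M. Different patterns therefore give the same coefficient:

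- 0.2/0.2/0.2 (pure prognosis) gives 0.2, and 0/0.3/0.3 (both trainings moderated) gives 0.6/3 = 0.2.
- 0.1/0.1/0.1 gives 0.1, and 0/0.3/0 (one training moderated) gives 0.3/3 = 0.1.
- 0/0.3/−0.3 (opposite moderation) gives 0.

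**3. Size, by illustration.** The assumptions, none of which is in the documents, are: the slopes; a residual SD of change of 1; a pooled model with arm dummies plus the predictor. The comparison is the same model with two predictor-by-arm terms, tested with a 2-df F test at .05. There are 100 per arm. Except in the second row, the rates come from 4000 simulated trials per scenario.

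| Slopes (waitlist / socio-emotional / mindfulness) | Regression as written | Interaction test |
|---|---|---|
| 0 / 0 / 0 | 5.0% | 5.4% |
| 0.1 / 0.1 / 0.1 | about 41% | about 5% |
| 0.2 / 0.2 / 0.2 | 93.0% | 5.2% |
| 0 / 0.3 / −0.3 | 5.7% | 96.8% |
| 0 / 0.3 / 0 | 40.6% | 57.1% |
| 0 / 0.3 / 0.3 | 91.6% | 56.8% |

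**4. Cross-check by formula.**

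- Common slope, λ = 300 · b². For b = 0.1, λ = 3.0 and F(1, 296) power is 0.41, which is the figure in the second row. For b = 0.2, λ = 12.0 and power is 0.93.
- Interaction, λ = 100 · Σ(b_i − mean)². For 0/0.3/−0.3, λ = 100 × (0 + 0.09 + 0.09) = 18 and F(2, 294) power is 0.97. For 0/0.3/0, λ = 100 × (0.01 + 0.04 + 0.01) = 6 and power is 0.58. The pattern 0/0.3/0.3 also gives λ = 6.

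These agree with the simulation.

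**The case against.** The strongest defence is the plan's own wording. It speaks of traits moderating change, and it says that the phase 1 factor scores will be used in the mixed-effects approach of the current phase. That mixed model contains time by group, so an interaction may be what the authors have in mind. The article also refers the reader to a preregistration for the detailed hypotheses, and nothing in it excludes an interaction. A reader might therefore infer from the written regressions that the plan rules out any test of differential benefit. The documents do not support that. What stands is that the sentences that define the models, for all three families of predictor, are plain regressions, and that what is said to be moderated is pre-post change and not the group effect on change.

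Four further points deserve weight.

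- The analyses are labelled exploratory in the Introduction and in the analysis plan, and they do not touch the main group-by-time tests. That limits the severity. It does not excuse estimating a different quantity, and the question in the Discussion carries no such label.
- Pretest level is controlled by autoregressive paths, so it would be wrong to say that regression to the mean is ignored. The adjustment reduces it. It does not remove other natural change shared with the waitlist arm, and it creates no treatment contrast.
- The pooled three-arm model is an inference, because these sections do not say how group enters. If arms were modelled separately, opposite slopes would be visible, but a formal comparison between arms would still be needed.
- Equal and opposite slopes are the worst case, because they cancel by construction. When only one training is moderated, the written regression still rejects in about 40% of trials, so it is not blind to moderation in general.

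**Conclusion.** The mismatch between aim and model is real. The plan asks who responds better, and to which training, and then writes regressions that estimate who changes more. Taken as written, a significant coefficient cannot separate prognosis from differential response: a rejection rate of about 92% under 0/0.3/0.3 and of 93% under 0.2/0.2/0.2 come from the same expected coefficient. The identity in step 2 needs only equal arms and a common slope. The percentages rest on the assumed slopes, the pooled model and a residual SD of 1, and are illustrations only.

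This should be corrected before analysis, but it concerns exploratory secondary analyses. The sample size of 297 is correct for the test it was planned for.

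**What to change.** In the section on prediction of pretest and intervention-related changes, and in the section on background, context and socio-demographic variables:

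- Add predictor-by-socio-emotional and predictor-by-mindfulness terms to the latent change models, with the waitlist arm included. The equivalent in the mixed model is time by group by predictor.
- Base every statement about response or benefit on the 2-df interaction test, followed by the contrast of slopes between the two trainings.
- Label the predictor's main effect on change as prognostic.
- Keep these analyses explicitly exploratory, and word question (b) in the Discussion the same way.

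The cost is two model terms per predictor and no new data. The downside is precision: with 100 per arm, power is about 57% for a slope of 0.3 SD in one training only (assumed), so fewer predictors will be reported as positive.
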